| **2.1**  **Research question/objective(s) of the study** | The aim is to assess the association between antibiotic use and risk of subsequent urinary tract infections in adults.  ***Background***  Urinary tract infections (UTIs) encompass a spectrum of infectious syndromes that affect the urinary tract anywhere from the urethra to the kidneys and are one of the most common infections, particularly in primary care (Al Hawati, Blair & Larnard). In 2023, the UTI incidence in primary care was 20 cases per 1.000 registered men and 117 cases per 1.000 registered women (Nivel, 2024). Not only is the UTI incidence higher in women than men, it also increases with age (Ahmet et al., 2018).  Women are particularly susceptible due to the close proximity of the rectum to the urethra as well as a relatively short urethral length (Li & Leslie, 2023). It is reported that 50-60% of women have at least one UTI in their lifetime (Al Hawati, Blair & Larnard, 2023). Most UTI are caused by bacteria from the gut  (Worby et al. 2022).  Most patients with UTIs can be treated relatively simple with oral antibiotics, although treatment failure occurs. Around 20-30% of women with an initial UTI will experience a recurrent UTI within 3-4 months of initial infection (Foxman, 2003). Furthermore, some UTIs can become complicated through a pyelonephritis, prostatitis, and urosepsis, which are associated with morbidity and mortality (Sabih & Leslie, 2023).  A healthy vaginal microbiota is low-diverse and dominated by *Lactobacillus crispatus*.  Vaginal lactobacilli have been touted to prevent invasion of uropathogens, for instance by creating an acidic environment. Disruption of the vaginal ecosystem, causing an overgrowth of anaerobic bacteria or yeasts, increases the risk of vaginal infections such as sexually transmitted infections (Stapleton, 2016, Herthelius 1988). Conversely, treatment that restores a Lactobacillus-dominated microbiota is associated with lower risk of recurrent UTIs. Usage of antibiotics can alter the microbial community (Chee, Chew & Than, 2020).  In pre-menopausal women, factors related to sexual behaviour are major risk factors for UTIs. These include: having a new sexual partner, increased frequency of sexual intercourse as well as the use of spermicide-containing contraceptives (Hooton, 2001). Sexual behaviour is less firmly associated with UTIs in post-menopausal women, where age-, hormonal- and disease-related urogynaecology and immune factors play a more prominent role. An increased postvoid residual urine volume, the presence of bladder prolapse and urinary incontinence have been associated with UTIs (Athanasiou et al., 2010). Antibiotic use or treatment of asymptomatic bacteriuria has also been associated with the development of UTIs (Cai et al., 2014, Smith et al. 1997).  To date, only one small-scale study has been conducted on this subject, which indicated a potential correlation between antibiotic use and an elevated risk of urinary tract infections in pre-menopausal women (Smith et al. 1997). To our knowledge, there are no studies whether this also holds for postmenopausal women and men.  In this study, we would like to evaluate whether different antibiotics (either to treat UTI or other infections) are associated with increased risk of UTI in premenopausal women, postmenopausal women and men. If this association can be confirmed, the next would be to study effective preventive measure for an UTI. This would be highly beneficial, as urinary tract infections represent a significant burden for patients, while antibiotic use is also the major contributing factor to the development of antibiotic resistance. |

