| --- | --- |

1. **Study design**

| **3.1**  **a. General description of the study design** | This research project will use the data infrastructure Extramural Leiden Academic Network (ELAN).  ELAN provides access to and the use of pseudonymized healthcare data from various cooperating partners such as healthcare data of general practitioners. The study period concedes 2014-2024.  ***Question***  Is antibiotic use associated with increased risk for urinary tract infection in adults?  Further explorations will be done to what extent the increased UTI risk of antibiotic use holds for:   - Different antibiotics or antibiotic classes - Men versus women - Post- versus Premenopausal women - Indication for antibiotic treatment (excluding UTI’s)   A self-controlled cases series (SCCS) design will be employed to establish the risk for developing an UTI within 3 months after antibiotic treatment compared to patients with an UTI who did not receive an antibiotic treatment. With the SCCS design, patients will be their own control.  The primary endpoint is risk of a UTI within 3 months after initiation of antibiotic treatment computed as an odds ratio.  An antibiotic treatment is defined as the exposure. An UTI between 2 weeks and 3 months after antibiotic treatment is defined as an event. The first 2 weeks after start of the treatment, patients are still somewhat protected by the antibiotic use against a new infection. And if a new antibiotic treatment is needed within 2 weeks after start of treatment, this is considered as treatment failure of the initial treatment.  Descriptive analysis will be performed for exposures, outcomes and covariables for the whole population of analysis and stratified by antibiotic use or not.  Multivariable logistic regression analysis will be performed to assess whether there is an association of antibiotic use with developing a UTI within 3 months after initiation of treatment. First a crude model will be used followed by confounder adjusted models. Confounders are season variability (Winter, spring, summer and autumn) and risk factors for UTI and selected based on theory or literature (Tj VanderWeele 2019). Risk factors are a history of an UTI, urine incontinence, urolithiasis, pregnancy, urine catheter, anatomical / functional abnormality urinary tract, immunocompromising comorbidities such as HIV/AIDS ,Type 2 Diabetes Mellitus.  **Subgroup analysis**  Subsequently, subgroup analysis will be performed to examine whether the association differs upon specific type of antibiotic treatment. For each subgroup, we will calculate an odds ratio for an UTI after antibiotic treatment. Subgroups are antibiotic(group)s, gender and age, type of infection and social determinants .  *Most used antibiotic(group)s in primary care*:   - Amoxicillin - Amoxicillin/clavulanic acid - Flucloxacillin - Tetracyclines - Macrolides - Fluoroquinolones - Trimethoprim - Co-trimoxazole - Fosfomycin - Nitrofurantoin   *Type of infection*   - All infections - UTI - non-UTI (all other infections)   *Gender and age*   - Men - Premenopausal women, defined as < 50 years of age - Postmenopausal women, defined as ≥ 50 years of age   *Social determinants*   - Socio-economic status (SES) - Migrant background |

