| **4.10**  **If coding takes place: when will coding occur, by whom, and in what manner?** | Coding is done by STIZON and CBS |
| **4.11**  **Has a notification of the intended data processing been submitted via:**  <https://www.albinusnet.nl/weten-en-regelen/juridische-zaken/privacy/meldenverzamelenonderzoeksdata/>**?** | Yes |
| **4.12**  **If applicable: where will the coded data be stored, and who will have access to the coded data?**  **If applicable: where will the uncoded data be stored, and who will have access to the uncoded data?** | The coded data is stored, and a specific research folder assigned to the department disk (I: \) of PHEG. Only the researchers involved ([name] and [name]) and the PHEG data manager have access to this folder.  There is no storage of uncoded data. |
| **4.13**  **What technical and organizational measures have been taken to prevent loss, theft, or unauthorized use of the research data? For example, is a data safe being used?** | The data never physically leaves the research folder of the LUMC or the remote access CBS environment and see 4.12. |
| **4.14**  **By whom is the code key managed?** | STIZON. |
| **4.15**  **Will (research) data be shared with another institution(s) within the Netherlands and/or the EU?** | No. |
| **4.16**  **a. Will (research) data be shared with another institution/organization outside the EU?**  **b. Will the relevant patients be asked for consent to share their personal data with a country outside the EU?** | No.  Not applicable. |
| **4.17**  **How long will the (research) data be retained? If the data will be kept for longer or shorter than the standard retention period of 15 years, please explain why.** | After processing, the research data is returned to ELAN in accordance with the data transfer agreement. The LUMC department PHEG will keep the research data for 15 years. |

1. **Research population**

| **5.1**  **Inclusion criteria** | Adults patients 18 year and older with an acute UTI and registered at an GP office for a least 1 year |
| --- | --- |
| **5.2**  **Exclusion criteria** | Patients younger than 18 years of age.  Patients with antibiotic prophylaxes  UTIs are excluded as an event if   - During pregnancy - within 3 months after giving birth - within 1 year prior to an UTI (wash-our period) |

1. **Statistical analysis**

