| **6.1**  **a. Primary outcome**  **b. Secondary outcome** | ***Primary outcome***  What is the association of antibiotic use for any infection with risk for urinary tract infection in adults?   - Odds ratio for an UTI after antibiotic use in the preceding 3 months   - Per infection group, antibiotic for     - All infections     - An UTI     - An infection expect UTI’s   - Per antibiotic (group)   - Per patient group     - Men     - Women < 50 years of age     - Women ≥ 50 years of age   - Social determinants     - SES     - Migrant background   - Combinations of each subgroup   ***Secondary outcome***   - Hazard ratio for an UTI after antibiotic use in the preceding 3 months   - Per infection group, antibiotic for     - All infections     - UTI     - non-UTI   - Per antibiotic group   - Per patient group     - Men     - Women < 50 years of age     - Women ≥ 50 years of age   - Social determinants     - SES     - Migrant background   - Combination of each subgroup - Incidence of an UTI per month |
| --- | --- |
| **6.2**  **a. Statistical analysis primary outcome**    **b. Statistical analysis secondary outcome** | ***Primary outcome***  The Odds ratio for an UTI after antibiotic treatment the preceding 3 months will be calculated through a logistic regression model.  Risk factors and season variability are defined as confounders in this logistic regression model. Risk factors are a history of an UTI, urine incontinence, urolithiasis, pregnancy, urine catheter, anatomical / functional abnormality urinary tract and Type 2 Diabetes Mellitus. An Odds ratio for an UTI will be attributed to each confounder based on a critical literature appraisal.  ***Secondary outcome***  Cox proportional hazard regression models will be used to examine the associations between an UTI after antibiotic treatment the preceding 3 months.  Survival time (in days) was defined as the period between 14 days after the start of the antibiotic treatment and an UTI. The hazard ratio will be adjusted with the previous described confounders (see primary outcome).  The incidence of each UTI will be calculated for each month during 10 years to examine the season variability. |

1. **Appendices and references**

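### Section 5.2 words the wash-out forward in time, so it drops a UTI because a later one follows; reversing it also requires a separate event rule for the planned UTI-indication analysis

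*Protocol*

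**What the plan says.** Section 5.2 lists three conditions under one stem, "UTIs are excluded as an event if". The first two are pregnancy and the 3 months after giving birth. The third is "within 1 year prior to an UTI (wash-our period"). The wash-out is stated nowhere else in the protocol.

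Three other places bear on it:

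- **5.1** requires patients to be "registered at an GP office for a least 1 year".
- **3.1** sets the risk window: "An UTI between 2 weeks and 3 months after antibiotic treatment is defined as an event". It also lists UTI as one of the infection types for subgroup analysis.
- **6.1** gives the primary outcome as "Odds ratio for an UTI after antibiotic use in the preceding 3 months", to be reported for antibiotics given for all infections, for a UTI, and for other infections.

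**The concern.** The stem makes the UTI itself the thing excluded, and the third bullet says when: if it falls in the year before another UTI. A wash-out normally works the other way, and a UTI fails to count as new because another came before it.

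The first two bullets can be judged on the day of the UTI. The third cannot. Whether a UTI counts would depend on what happens to the patient in the following 365 days, and for UTIs in the last year of data the condition cannot be fully checked. A programmer who follows the text and one who follows the label would analyse different sets of primary events.

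**Working it through.** The protocol states no event count or sample size tied to this rule, so there is no figure of its own to reproduce. The check applies both readings to event dates.

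**The two rules, with a 365-day period**

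- As written: drop a UTI if another UTI follows within 365 days.
- Look-back: drop a UTI if another UTI was recorded in the preceding 365 days.

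**Worked example.** UTIs on days 100, 160, 300 and 1200; the gaps are 60, 140 and 900 days.

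| Rule | Dropped | Kept |
|---|---|---|
| As written | 100, 160 | 300, 1200 |
| Look-back | 160, 300 | 100, 1200 |

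In any run of UTIs with gaps of at most a year, the written rule keeps the last and the look-back keeps the first. Each keeps one per run, so the number of events is the same.

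**How many kept events differ.** From section 2.1: "20 cases per 1.000 registered men and 117 cases per 1.000 registered women", that is 0.020 and 0.117 per person-year, and "Around 20-30% of women with an initial UTI will experience a recurrent UTI within 3-4 months of initial infection". The protocol does not say how much UTI rates vary between patients, so that is assumed. UTIs were simulated as Poisson with gamma-distributed patient rates, with every UTI treated on its date and no antibiotic effect.

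*Set 1: 10 years, heterogeneity simply assumed.*

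| Rate per year | Gamma shape | UTIs kept (either rule) | Kept events in common | Different |
|---|---|---|---|---|
| 0.117 | no heterogeneity | 90% | 90% | 10% |
| 0.117 | 0.3 | 68% | 74% | 26% |
| 0.117 | 0.1 | 48% | 64% | 36% |
| 0.020 | 0.1 | 83% | 85% | 15% |

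About 10-14% of the events kept by the written rule lie in the final year, where the rule cannot be fully checked.

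*Set 2: 11 years, shape k fitted to the recurrence quoted above.* Solve (1 + μt/k)^−(k+1) = 1 − r for r = 20% at 4 months, 25% at 3.5 months and 30% at 3 months. This gives k = 0.19, 0.12 and 0.07 at μ = 0.117, and k = 0.03, 0.02 and 0.01 at μ = 0.020. Applying the recurrence figure for women to the rate for men is a further assumption. The two rules then have 60-70% of kept events in common, so 30-40% differ.

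**Does the direction itself bias the estimate?** Set 2, true ratio 1, exposed days 14-91 after a treated UTI:

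| Event rule | Kept UTIs that are exposed | Crude rate ratio | Within-person ratio (conditional Poisson) |
|---|---|---|---|
| No wash-out | 13-28% | 2.05-3.24 | 0.86-0.93 |
| As written | 8-13% | 1.24-1.33 | 0.86-0.94 |
| Look-back, 1 year | 0% | 0 | not estimable above 0 |

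The crude excess over 1 is largest with no wash-out, so it comes from the assumed differences between patients and not from the direction of the rule.

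**Why the look-back gives zero.** Let a UTI be recorded and treated on day s. An exposed event falls on day u with 14 ≤ u − s ≤ 91. A look-back of W days drops u when u − s ≤ W.

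- W = 365, or any W of about 91 or more: every such u is dropped.
- W between 14 and 91: only events later than s + W survive.
- W no greater than 14: essentially none is lost.

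This holds when the look-back refers to any recorded UTI. It is approximate if treatment starts some days after the UTI is recorded.

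**The case against.** The strongest reply is that nobody would program the literal text. The list in 5.2 is telegraphic, the bullet misspells its own label, and a loose reader takes it to mean that a UTI is excluded if there was another in the year before. The label and the registration requirement support that reading. This stands as far as intent goes, and it is why the point concerns wording and not a deliberate design choice. It does not remove the point: the protocol is the reference for the event definition, its only statement of the rule runs the other way, and the correction is one sentence.

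A reader might also infer from the crude ratio of about 1.3 that the written rule inflates the antibiotic effect by some 30%. The material does not support that. With no wash-out the same simulation gives 2 to 3, so the written rule lowers the crude ratio. In a within-person analysis, which 3.1 names as the design, the written rule and no wash-out give nearly the same result.

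Nor should one argue that follow-up contacts coded as UTI would be kept in place of true onsets. The mechanism is conceivable, but the protocol says nothing about how often such contacts are coded U70 or U71.

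Finally, it is fair to object that a simple reversal does harm of its own: it empties the UTI-indication stratum. That stands in full, and the fix has to deal with it.

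**Conclusion.** The point holds as an error of wording in a rule that defines the primary event set. As written, 5.2 selects events on the future and keeps the last UTI of a cluster, against the evident intent of a look-back. That conclusion rests on the text alone.

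The size is illustrative. Roughly 10-40% of kept events differ between the two readings, depending on the assumed heterogeneity and recurrence, with the number of events unchanged. No direction or amount of bias in the primary odds ratio is established.

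The conflict that a one-year look-back creates with the UTI-indication analysis follows from the window definitions and does not depend on the simulation.

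**What to change.** - **Reword the third bullet of 5.2**, for example: a UTI is not counted as a new event when another UTI (U70/U71) was recorded in the preceding wash-out period. Add that no UTI is excluded because of a later one.
- **In the same edit, reconcile the wash-out with the UTI-indication analysis in 3.1 and 6.1.** Either give that stratum its own event rule, such as a short gap separating episodes that is no longer than the 2-week start of the risk window, or drop the stratum. A gap of that length fits 3.1, which already treats a new antibiotic course within 2 weeks as failure of the first. The same choice decides which UTIs can count in the all-infections analysis, so state it there too.

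The cost is a sentence or two in 5.2, a matching line in 3.1 and 6.1, and the corresponding event-derivation code. No new data are needed. The decision on the stratum should be made before the analysis is run.

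### Read as a look-back, the 1-year UTI wash-out in Section 5.2 leaves no countable events for the UTI-indication contrast planned in Sections 3.1 and 6.1

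*Protocol*

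**What the plan says.** Section 5.2 lists conditions under the lead-in "UTIs are excluded as an event if". The third is "within 1 year prior to an UTI (wash-our period"). Section 5.1 requires patients to be "registered at an GP office for a least 1 year".

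Section 3.1 fixes the outcome window: "An UTI between 2 weeks and 3 months after antibiotic treatment is defined as an event". Its subgroup list divides antibiotic courses by type of infection into all infections, UTI and "non-UTI (all other infections"). Section 6.1 repeats this division under the primary outcome, "Odds ratio for an UTI after antibiotic use in the preceding 3 months", and again for the secondary hazard ratio. Section 3.5 takes the indication from the ICPC diagnosis linked to each prescription, with U70 and U71 as the UTI codes.

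The aim in Section 2.1 covers both indications: "we would like to evaluate whether different antibiotics (either to treat UTI or other infections) are associated with increased risk of UTI". The background there also says "Around 20-30% of women with an initial UTI will experience a recurrent UTI within 3-4 months of initial infection". No exception to the wash-out is stated for the UTI stratum.

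**The concern.** The wash-out and the outcome window work against each other. A course in the UTI stratum has, by definition, a UTI behind it. A rule that discards any UTI with another UTI in the year before it discards every event that course could produce, including the early recurrences that the background cites.

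Three things are at stake. A contrast listed under the primary outcome may have no events; Section 4.9 also bars output from cells with fewer than ten units, so it could not be exported. Subgroups for antibiotics prescribed mainly for UTI lose events to the extent of that use, which the protocol does not quantify. And the pooled all-infections estimate may carry exposed time in which no event can be counted.

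**Working it through.** The protocol gives no expected odds ratio or event count on this point, so there is no figure to reproduce.

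**Step 1: window logic, with no assumed rates.** The event window is day 14 to about day 90 after the antibiotic starts (3.1). The wash-out is 365 days (5.2). Since 90 < 365, an event after a UTI-indicated course always lies inside the wash-out of the treated UTI. This holds even if the prescription lags the UTI record by up to 365 − 90 = 275 days. On the look-back reading the stratum has zero events at any incidence.

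**Step 2: pooled estimate.** Suppose only events are removed. Let θ be the true ratio and f the share of exposed time that follows UTI antibiotics. That share contributes no events, so the pooled ratio is about θ × (1 − f). It is below 1 only if f > 1 − 1/θ:
- θ = 1.5: f above 33%
- θ = 2: f above 50%
- θ = 3: f above 67%

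**Step 3: simulation.** 15,000 people were followed daily for 10 years, with UTI risk varying between people, every UTI treated, and an exposed window of days 14 to 90. The rate of 0.117 UTIs per year is the figure for women in Section 2.1. The rate of 0.30, the non-UTI course rates and θ are assumptions. Results are crude rate ratios, not the logistic odds ratio of Section 6.2.

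| θ | UTIs/yr | Non-UTI courses/yr | f | θ(1 − f) | Pooled, look-back | Non-UTI, look-back | Ratio with person-time also removed | UTI-stratum events: no wash-out → look-back |
|---|---|---|---|---|---|---|---|---|
| 1.0 | 0.117 | 0.30 | 0.28 | 0.72 | 0.71 | 0.99 | 0.99 | 738 → 0 |
| 1.5 | 0.117 | 0.30 | 0.30 | 1.05 | 1.05 | 1.50 | 1.50 | 1,163 → 0 |
| 1.5 | 0.30 | 0.30 | 0.52 | 0.72 | 0.74 | 1.53 | 1.52 | 7,061 → 0 |
| 2.0 | 0.117 | 0.30 | 0.30 | 1.40 | 1.40 | 2.00 | 2.00 | 1,589 → 0 |
| 2.0 | 0.30 | 0.15 | 0.69 | 0.62 | 0.63 | 2.01 | 2.01 | 9,454 → 0 |

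The factor (1 − f) presumes that non-UTI courses fall in washed-out time as often as unexposed time does, as they do here. In the opposite limit, where they never do, the reference rate also falls. With n UTIs in 3,650 days and 90-day windows, the ratio becomes θ(1 − f)/(1 − 275n/U), with unexposed days U = 3,650 − 90n/f. For θ = 1, f = 0.2, n = 3: U = 2,300 and the ratio is 0.8/0.641 = 1.25. So (1 − f) is a guide to size, not a bound.

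**Step 4: other readings of 5.2, same scenarios.**
- Wash-out counted only from the last counted event: 22 to 602 UTI-stratum events remain, but the stratum ratio is 0.07 to 0.35.
- Strictly literal wording (drop the earlier UTI of a pair within a year): 548 to 4,053 events remain, but whether a UTI counts depends on what happens afterwards.
- No wash-out: the stratum has events, but its crude between-person ratio is 2.04 when the truth is 1, because UTI-prone people are over-represented.

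**The case against.** The strongest reply is that the wording of 5.2 is garbled, and a reader who infers that the UTI stratum is empty on any reading goes too far. That stands: only the look-back gives exactly zero. The look-back is nevertheless the likeliest reading, since both the wash-out label and the one-year registration rule point to it. The literal reading carries its own defect.

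Second, the protocol nowhere says that person-time after a UTI stays in the analysis, and such handling is often left to an SAP. This stands in part. Excluding UTIs as events implies that only events go, but does not state it, so attenuation of the pooled estimate is conditional. The conflict over the UTI stratum is not: the protocol itself fixes both the exclusion and the contrast.

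Third, a reader might infer that the main result will reverse. The documents do not support that, because they give neither f nor θ. With θ = 1.5 and the women's rate, within-person conditional rate ratios of about 0.86 can be produced, but the crude ratio under similar assumptions is about 1.05. With the men's rate in Section 2.1 (20 per 1,000) the conditional ratio is 1.16, and with θ = 2.0 at the women's rate it is 1.19.

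Fourth, a wash-out can be a deliberate way to separate new UTIs from relapse, and one line of Section 3.1 does plan the exploration by indication with UTIs left out. That fits the non-UTI contrast, which is unharmed. It does not fit the UTI stratum that 3.1 and 6.1 also list.

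**Conclusion.** The point holds in a bounded form. On the look-back reading, Section 5.2 removes every event from the UTI-indication stratum, so the odds and hazard ratios planned for it in 3.1 and 6.1 cannot be estimated. That follows from 90 days being less than 365 and needs no assumed rate. On the literal reading the stratum survives, but events are selected on a later UTI. Either way, 5.2 must be reconciled with 3.1 and 6.1.

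The effect on the all-infections estimate is conditional on UTI-antibiotic windows staying in the exposed time. Its size is then roughly a factor (1 − f), for example 1.5 becoming 1.05 at f = 0.30, provided non-UTI courses are spread evenly over washed-out and other time. A fall below 1 is possible but not established. The non-UTI contrast is not affected: its simulated ratio stayed at 0.99 to 2.01 for true values of 1.0 to 2.0.

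**What to change.** Reword 5.2 as an explicit look-back: a UTI counts as an event only if there was no UTI in the preceding 365 days. Remove the person-time and exposure windows in that year together with the events, and do the same for pregnancy and the 3 months after birth. Remove the UTI-indication stratum from every analysis that uses the wash-out, and state that these analyses concern non-UTI antibiotics.

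If the UTI-indication question is kept, analyse it separately without the wash-out, with a stated definition of a new UTI episode and a within-person (SCCS) comparison. The 2-week gap in 3.1 does not supply that definition, because it describes treatment failure. The within-person comparison matters because a crude between-person ratio is biased upward by UTI-prone patients, and a robust variance does not correct that.

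The cost is one rewritten rule, data-step code on existing data and one additional analysis. The wash-out analysis will have less follow-up, and fewer events than an analysis without it: in the simulated scenarios 19% (15,561 to 12,562) to 46% (44,720 to 24,040) fewer.

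### The lead primary exposure includes antibiotics given for a UTI, so the outcome triggers the exposure and post-UTI recurrence falls inside the risk window

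*Protocol*

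**What the plan says.** - **Primary question (6.1):** "What is the association of antibiotic use for any infection with risk for urinary tract infection in adults". Below it are three infection groups: all infections, UTI, and infections other than UTI. No lead is named among them beyond the any-infection wording of the question.
- **Exposure (3.1):** "An antibiotic treatment is defined as the exposure", with no limit on indication. Section 2.1 says the antibiotics of interest are those given "either to treat UTI or other infections".
- **Event (3.1):** "An UTI between 2 weeks and 3 months after antibiotic treatment is defined as an event".
- **Design (3.1):** "A self-controlled cases series (SCCS) design will be employed to establish the risk for developing an UTI within 3 months after antibiotic treatment". Patients act as their own controls.
- **Recurrence (2.1):** "Around 20-30% of women with an initial UTI will experience a recurrent UTI within 3-4 months of initial infection". The same section says that most UTIs can be treated with oral antibiotics.
- **Indication lists (3.1):** the list of explorations has "Indication for antibiotic treatment (excluding" UTIs), whereas the subgroup list later in the section includes UTI as a type of infection.
- **Possible safeguards:** history of UTI is a listed confounder (3.1, 6.2), with no look-back or timing. Section 5.2 has a 1-year wash-out for UTIs as events; its wording is ambiguous and says nothing about person-time.

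**The concern.** An SCCS compares event rates within a person between exposed and unexposed time. It removes characteristics that stay fixed. It does not remove a temporary rise in risk, and it requires that an event leave later exposure unchanged. Both limits matter when UTI courses count as exposure.

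First, a UTI leads to a course, so each treated UTI creates its own exposed window. Second, a person who has just had a UTI is at raised risk of another for some months, and that period overlaps the risk window. The model cannot tell an effect of the drug from the course of the infection it was prescribed for. A history-of-UTI covariate without timing does not help much, because every included patient has a UTI (5.1) and what matters is how recent it was. Nor is there much of an untreated group among UTIs to compare with.

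At stake is the reading of the headline result. Section 2.1 would use a confirmed association as the reason to study preventive measures. An estimate that can move away from 1 in either direction without any drug effect is a poor basis for that.

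**Working it through.** The protocol states no sample size, event count or expected effect, so there is no figure of its own to reproduce. Both checks ask what the planned contrast shows when antibiotics have **no** effect.

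**1. Within-person (SCCS) simulation**

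Assumed inputs, not in the document: base UTI rate 0.10 per year, 0.3 non-UTI courses per year, every UTI treated, and UTI hazard multiplied by m until day 120 after a UTI. From 3.1: risk window about days 14 to 90. The estimate is the conditional Poisson rate ratio.

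Implied recurrence over days 14 to 120 is 1 − exp(−0.10 × m × 106/365).

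| m | Implied recurrence | All infections | Non-UTI courses only |
|---|---|---|---|
| 1 | 2.9% | 0.78 to 0.79 | about 1.0 |
| 3 | 8.3% | 1.13 to 1.15 | about 1.0 |
| 6 | 16.0% | 1.73 | 0.96 |
| 7 | 18.4% | 1.95 to 1.97 | about 1.0 |
| 10 | 25.2% | 2.63 | 1.04 |

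Across these runs the non-UTI estimates lie between 0.96 and 1.04. Another run at 6-fold, differing in detail, gave 2.39 for all infections and 0.99 for non-UTI courses.

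The first row shows the effect of event-dependent exposure alone: a case's UTI is followed by exposed time that often holds no further event, which pulls the ratio below 1. Excess recurrence then pushes it up.

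Which row applies depends on the base rate. To reach the 20 to 30% in 2.1 over those 106 days, m = −ln(1 − R) × 365/(base × 106):
- base 0.10 per year: m = 7.7 (R = 20%) to 12.3 (R = 30%);
- base 0.30 per year: m = 2.6 to 4.1.

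The document does not give the base rate in a UTI-only cohort. The table was run at 0.10 only.

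**2. Odds-ratio scale, closed form**

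Section 6.2 plans a logistic model, so a simple unmatched check is added.
- Recurrence in a 76-day window: 20% in 4 months gives 1 − exp(ln(0.8) × 76/121.6) = 13.0%; 30% in 3 months gives 1 − exp(ln(0.7) × 76/91.2) = 25.7%.
- Background, assuming 0.30 per year in this cohort: b = 1 − exp(−0.30 × 76/365) = 6.06%.
- With a share s of courses given for UTI (assumed), OR = odds(s·p + (1 − s)·b)/odds(b).

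Example, s = 25% and p = 13.0%: 0.25 × 0.130 + 0.75 × 0.0606 = 0.0780; odds 0.0845; divided by 0.0645 gives 1.31. The ranges over p are 1.1 to 1.4 at s = 10%, 1.3 to 1.9 at 25% and 1.6 to 2.9 at 50%. This check ignores self-matching, so it shows only the upward part.

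**3. The wash-out in 5.2, no drug effect, 6- to 7-fold recurrence**

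| Reading | All infections |
|---|---|
| Literal: the earlier UTI is dropped as an event, its antibiotic still counts as exposure | 2.1 to 2.4 |
| UTI-free year required before each event, person-time kept | 0.40 to 0.59 |
| Events and person-time within a year after a UTI both removed | 0.96 to 1.05 |

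The last reading stayed at 0.99 to 1.08 in runs at 1-, 6- and 10-fold. Both UTI-free-year readings leave no exposed events in the UTI-antibiotic group that 3.1 and 6.1 plan to analyse: a UTI within 3 months of a course for a UTI cannot follow a UTI-free year.

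**The case against.** The case on the other side has four parts.

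**The non-UTI contrast is already planned.** It stands under the primary outcome in 6.1 with its own odds ratio. This is true and makes the remedy cheap. But it is one of three groups, and the question above them is worded for any infection.

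**The wash-out may remove the bias.** It does under one reading. The text does not say that person-time is removed, and that reading empties a stratum the plan intends to report. So it cannot be counted as a safeguard until it is reworded.

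**History of UTI is adjusted for.** Its definition could sit in an analysis plan that is not shown, and a well-timed covariate would help. As written, it has no timing, and treated UTIs have almost no untreated comparator.

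**Size and direction are uncertain.** This stands in full. Two stronger readings are tempting, and the documents do not support them:
- A reader might set the 20 to 30% recurrence against the general rate in 2.1 ("In 2023, the UTI incidence in primary care was 20 cases per 1.000 registered men and 117 cases per 1.000 registered women"). Over 3 to 4 months, 117 per 1,000 per year gives 2.9 to 3.8%, hence a ratio of roughly 5 to 10. That compares UTI patients with all registered women, whereas the study enrols only UTI patients and compares them with themselves. The recurrence figure may also already contain any drug effect, since most UTIs are treated.
- A reader might conclude that a positive result is certain without any drug effect. The simulations run from 0.4 to 2.6 depending on recurrence and on how the wash-out is read, so that does not follow.

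**Conclusion.** The concern holds. The any-infection exposure in 3.1 and 6.1 includes courses triggered by the outcome, which breaks an SCCS assumption and places post-UTI recurrence inside the risk window. With no antibiotic effect, the all-infection estimate is about 0.8 with no excess recurrence, 1.1 to 1.2 at 3-fold and 1.7 to 2.6 at 6- to 10-fold, against about 1.0 for non-UTI courses. These sizes assume 0.10 UTIs and 0.3 non-UTI courses per year and treatment of every UTI. The share of courses given for UTI and the cohort's base rate are not in the document. What does not depend on those figures is that the headline estimate cannot be read as an antibiotic effect, and that the wash-out as worded either fails to protect it or conflicts with the planned UTI-antibiotic group. The primary exposure is fixed in the protocol itself, so this is not a detail left to an analysis plan. It should be settled before the analysis.

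**What to change.** 1. In 3.1 and 6.1, name antibiotics with a non-UTI ICPC indication as the single lead primary exposure.
2. Give the window after a UTI course its own model term, so that it is neither exposed nor reference time.
3. Report the all-infection and UTI-indication estimates as secondary, described as recurrence after a treated UTI and not as an antibiotic effect.
4. Reword the wash-out in 5.2 to say which UTI is dropped, what happens to the person-time and what happens to the antibiotic course, and check that the result is compatible with the strata in 6.1.
5. Make the two indication lists in 3.1 agree.

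The cost is modest. The diagnosis code for each prescription is already extracted (3.5), and the contrast is already listed in 6.1. The price is fewer exposed events in the lead analysis and wider intervals for drugs used mainly for UTI.
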